## Abstract

**Background:**

Acute coronary syndrome(ACS) is the leading cause of mortality and disability worldwide. Immune response has been confirmed to play a vital role in the occurrence and development of ACS. The objective of this prospective, multicenter, observational study is to define immune response and their relationship to the occurrence and progressive of ACS.

**Methods:**

This is a multicenter, prospective, observational longitudinal cohort study. The primary outcome is the incidence of major adverse cardiovascular events (MACE) including in-stent restenosis, severe ventricular arrhythmia, heart failure, recurrent angina pectoris, and sudden cardiac death, and stroke one year later after ACS. Demographic characteristics, clinical data, treatments, and outcomes are collected by local investigators. Furthermore, freshly processed samples will be stained and assessed by flow cytometry. The expression of S100A4, CD47, SIRPα and Tim-3 on monocytes, macrophages and T cells in ACS patients were collected. Follow-up: during hospitalization, 3, 6 and 12 months after discharge.

**Discussion:**

It is expected that this study will reveal the possible targets to improve the prognosis or prevent from occurrence of MACE in ACS patients. Since it’s a multicenter study, the enrollment rate of participants will be accelerated and it can ensure that the collected data are more symbolic and improve the richness and credibility of the test basis.

**Ethics and dissemination:**

This study has been registered in Chinese Clinical Trial Registry Center. Ethical approval was obtained from the Affiliated Hospital of Guizhou Medical University. The dissemination will occur through the publication of articles in international peer-reviewed journals.

**Trial Registration:**

Chinese Clinical Trial Registry: ChiCTR2200066382.

**Supplementary Information:**

The online version contains supplementary material available at 10.1186/s12872-023-03224-9.

## Background

Coronary heart disease (CHD) is the leading cause of death and morbidity worldwide, causing serious economic burden to the society, among which acute coronary syndrome (ACS) is a type of CHD with the most acute onset and the highest mortality [1]. ACS includes ST-segment elevation myocardial infarction (STEMI), non ST-segment elevation myocardial infarction(non-STEMI) and unstable angina (UA). Although reperfusion therapies such as percutaneous coronary intervention(PCI) have been widely applied and improved early survival, major adverse cardiovascular events (MACE) after ACS such as in-stent restenosis, severe ventricular arrhythmia, heart failure, recurrent angina pectoris, and sudden cardiac death, still need to be concerned [2].

Numerous studies indicated that inflammatory response after ACS is a precisely regulated process and is a significant link in the instability and development of atherosclerotic plaques which acts as a pivotal role in clearing cellular debris and recovery after ACS [3–5]. Dysregulation of inflammation or prolonged inflammation may lead to adverse cardiac remodeling and MACE [6].

The innate immune response and acquired immune response are primary part of the inflammatory process of ACS. Mononuclear phagocyte system (MPS) participates in the former response, including macrophages, monocytes and dendritic cells [7]. In addition, imbalance of necrotic cell clearance can lead to enlarged myocardial infarction [8]. T cells, nature killer T cells(NKT cells) and tim-3 (also known as CD366 or T-cell immunoglobulin and mucin containing Protein-3), which is a sign of T cell exhaustion, participate in the latter response [9–11].

Calcium ion is an important second messenger of cells, the calcium metabolism engaged in the progression of various cardiovascular diseases. S100A4, a calcium ion binding protein, is a member of the S100 protein family [12]. This calcium ion binding protein family has been proved to be involved in various biological processes, for instance, cell apoptosis, Ca^2+^ homeostasis and above all, inflammation [13]. In our previous study, results indicated that the expression of S100A4 elevated in peripheral leukocyte of ACS patients.

Based on the evidence discussed above, we assume that innate immune response and acquired immune response are both involved in the process of ACS, as well as calcium binding protein S100A4. Therefore, the characteristics of various subtypes of monocytes, macrophages and T cells in peripheral blood might differ and influence the prognosis in ACS patients. In order to explore the possible targets in these inflammatory cells that might improve the prognosis of ACS patients, we investigated the account and distribution of monocytes, macrophages, T cells, NKT cells and the expression of CD47, sirpα, tim-3 and S100A4 on these cells. Furthermore, we explored the correlation between these indexes and the incidence of MACE after 1 year in ACS patients by follow-up at four timepoint: during hospitalization, 3, 6 and 12 months after discharge. It may provide new therapeutic strategies for improving the prognosis of patients with ACS.

## Methods

### Aim of the study

To detect the characteristics of various subtypes of monocytes, macrophages, T cells and explore the expression of CD47, sirpα,S100A4 and Tim-3 on these cells in peripheral blood of ACS patients and investigate the relationship between them and the occurrence of MACE 1 year later.

### Study design and setting

This is a multicenter, prospective, observational, longitudinal cohort study that will be carried out between December 2022 to December 2024. Three centers participate in this study, including The Affiliated Hospital of Guizhou Medical University which is also the host of this study,  the First People’s Hospital of Guiyang and the Second People’s Hospital of Guiyang. The study will be conducted in accordance with the Declaration of Helsinki (as revised in 2013). Ethics approval for the trial was obtained only from the main center—Ethics Committee of The Affiliated Hospital of Guizhou Medical University (Medical Research Ethics Review 2022. No. 2022117 K). Written informed consent will be obtained from the patients. This study was registered at Chinese Clinical Trial Registry (ChiCTR) (No. ChiCTR2200066382). The outcomes will be assessed during hospitalization and at four follow-up times (during hospitalization, 3, 6, 12 months after discharge).

### Study populations

Patients who had been hospitalized in multicenter including Affiliated Hospital of Guizhou Medical University, the First People’s Hospital of Guiyang and the Second People’s Hospital of Guiyang from December 2022 to December 2023 and were diagnosed as ACS according to the guideline.

### Inclusion criteria

i) Patients initially diagnosed as ACS according to the 2020 European Society of Cardiology(ESC) guideline [14] and went through PCI. The diagnosis of acute myocardial infarction includes symptoms (like chest discomfort), electrocardiogram (ECG) showing that characteristic abnormalities include ST-segment and T-wave changes, and elevation of a cardiomyocyte biomarker especially high-sensitivity cardiac troponin T (hs-cTnT). The diagnosis criteria of UA is that history (such as risk factors for CHD), symptoms (initial or aggravation angina pectoris in 1 month), and ECG showing that ST-segment depresses or T wave changes without the elevation of cardiomyocyte biomarker; ii) Duration of onset of patients ≤ 2 weeks; iii) The range of age is 18–100 years old; iv) Patients who are willing to comply with the protocol, can understand the purpose of the study, voluntarily participate in the study or legal guardian signed the informed consent.

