### Consent

Patients who do not meet the exclusion criteria and who meet all inclusion criteria may participate in this study. Researchers of the study including [name] and [name] will screen eligible patients for ACS diagnosis in the Chest Pain Center of multicenter and communicate with them or their agents about the general content of the study. These patients have every right to choose to participate in the study or not. These patients or their agents will be fully informed that participation in the study will not affect normal diagnosis and treatment, will not increase the risk of participants, and that participation or non-participation in the study will not affect patients' normal medical interests. However, participation in this study may provide new hope for improving the prognosis of patients with ACS. In addition, when patients or their agents agree to participate in the study, they could to choose how the clinical outcomes will be observed in different time point: by telephone, inpatient and outpatient medical records, or by contacting our researchers themselves and indicating on their informed consent. The dissemination of the results will occur through the publication of articles in international peer-reviewed journals, once the results are published, patients and their representatives will be notified by text or phone within a year. Those who agree to participate will sign informed consent.

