#### Blood sample and data collection

Peripheral blood samples of these patients were obtained within 24 h of admission and collected in heparin anticoagulant tube (2–4 mL). Samples were placed at room temperature for testing within 24 h. Clinical data of patients such as age, gender, history of hypertension, coronary heart disease and diabetes mellitus, body mass index (BMI), white blood cell count, level of hemoglobin, platelet, creatinine, aspartate aminotransferase (AST), alanine aminotransferase (ALT), lipid profile, left ventricular ejection fraction, left ventricular end-diastolic volume etc. were collected. The results of coronary angiography were recorded as well.

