#### Follow-up

Patients will be followed up during hospitalization(t0), 3 months(t1), 6 months(t2) and 12 months(t3) after discharge through outpatient-clinic, hospitalization, telephone and other communication way. Content of follow-up is presented in Table 1.

**Table 1 Tab1:** Content of follow-up at different time points post-PCI

Assessments	t0	t1	t2	t3

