** LDL-C(≤ 1.4 mmol/L)**				
**Outcomes**				
In-stent restenosis				
Severe ventricular arrhythmia				
Heart failure				
Recurrent angina pectoris				
Sudden cardiac death				
No reflow				
Atrial fibrillation				
Death from other causes other than cardiac death				
Stroke/cerebrovascular accident				

Including daily living conditions (whether to follow a low-salt and low-fat diet, whether there is proper exercise, whether to quit smoking, drinking, etc.), and whether to use medications for secondary prevention for CHD, including antiplatelet agents, statins, angiotensin-converting enzyme inhibitor(ACEI)/angiotensin II receptor(ARB), β blocker, and whether the dose of ACEI/ARB and β blocker meets the recommended dose, blood pressure control(≤ 130/80 mmHg), blood glucose control(fasting blood glucose ≤ 6.0 mmol/L, 2 h postprandial blood glucose ≤ 11.0 mmol/L, or glycosylated hemoglobin ≤ 6.5%), control of low-density lipoprotein cholesterol(LDL-C) (≤ 1.4 mmol/L) and occurrence of MACE which including in-stent restenosis, severe ventricular arrhythmia, heart failure, recurrent angina pectoris, and sudden cardiac death. The content of follow-up also includes no reflow, atrial fibrillation, occurrence of death from other causes other than cardiac death, and stroke/cerebrovascular accident. The definition of all outcomes is presented in Table 2.

**Table 2 Tab2:** Definition of the outcomes

Events (during hospitalization or follow-up)	Definition
In-stent restenosis	In-stent restenosis is defined if it is observed during coronary angiography reexamination
Severe ventricular arrhythmia	Including ventricular tachycardia, ventricular fibrillation captured by ECG or ECG monitoring
Heart failure	The patients had typical symptoms of heart failure (such as chest tightness, dyspnea, etc.) combined with cardiac ultrasound suggesting decreased cardiac systolic or diastolic function or accompanied by elevated NT-proBNP
Recurrent angina pectoris	If symptoms that are similar or even aggravated to previous angina symptoms like location, time, and degree of pain still occur after PCI
Sudden cardiac death	Sudden cardiac death due to coronary heart disease
No reflow	No coronary reflow or slow flow is observed during PCI or coronary angiography reexamination
Atrial fibrillation	Paroxysmal or persistent atrial fibrillation captured by ECG or ECG monitoring

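### Entry requires completed PCI but the marker sample is timed only by admission, so the visible rules allow samples on either side of PCI and outcomes that precede the marker

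*Protocol article*

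**What the plan says.** All places are in the protocol article.

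- **Inclusion criteria, item i:** patients have ACS by the "guideline [14] and went through PCI". Item ii sets the limit on time since onset: "Duration of onset of patients ≤ 2 weeks".
- **Blood sample and data collection:** "Peripheral blood samples of these patients were obtained within 24 h of admission". This is the only marker draw described, and PCI is not mentioned in its timing.
- **Consent:** researchers "will screen eligible patients for ACS diagnosis in the Chest Pain Center", and participation is open to those who satisfy every inclusion criterion.
- **Aim of the study:** measure the immune markers and "investigate the relationship between them and the occurrence of MACE 1 year later".
- **Secondary outcomes and Table 2:** no reflow is a secondary outcome, defined as "No coronary reflow or slow flow is observed during PCI or coronary angiography reexamination". The header of Table 2 counts all events from the hospital stay onward.
- **Follow-up:** "Patients will be followed up during hospitalization(t0), 3 months(t1), 6 months(t2) and 12 months(t3) after discharge".
- **Sample size:** 50 STEMI, 50 non-STEMI and 50 UA patients.
- **Statistical analysis:** a univariate screen followed by stepwise logistic regression. The position of the sample relative to PCI is not named as a variable.

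**The concern.** The draw is the exposure measurement for the whole study. Its clock starts at admission, whereas eligibility and one secondary outcome are tied to PCI. Nothing in the visible text connects the two clocks.

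Three things are at stake.

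1. **Order of marker and outcome.** A marker measured after PCI cannot predict what happened at that PCI. The same holds for any in-hospital event before the draw.
2. **Comparability of samples.** The Background describes PCI as a reperfusion therapy, and the Discussion links the immune response to necrosis and ischemia–reperfusion injury. By the plan's own rationale, a sample before reperfusion and one after it may differ. If PCI timing differs between STEMI, non-STEMI and UA, so does sample position, and a marker difference may partly reflect the procedure.
3. **Entry after exposure.** A patient sampled before PCI satisfies item i only if PCI follows.

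This is distinct from time since onset: two patients sampled at the same interval from onset can be on opposite sides of PCI.

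**Working it through.** **Step 1: the timing rules side by side**

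| Element | Clock it is tied to | Section |
|---|---|---|
| Eligibility | PCI done | Inclusion criteria, i |
| Disease duration | Onset, up to 2 weeks | Inclusion criteria, ii |
| Screening | Diagnosis in the Chest Pain Center | Consent |
| Marker sample | Admission, up to 24 h | Blood sample and data collection |
| No reflow | PCI or repeat angiography | Table 2 |
| MACE components | Hospital stay or follow-up | Table 2 |

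**Step 2: what these rules allow.** Let S be the hours from admission to sample and P the hours from admission to index PCI. The stated constraints are S ≤ 24 and that PCI took place. Three cases comply.

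- (a) P < S ≤ 24: the sample is post-PCI. Index no reflow, and any MACE component before S, precedes the marker.
- (b) S < P ≤ 24: the sample is pre-PCI, and item i is not yet met at the draw.
- (c) P > 24: the sample is necessarily pre-PCI, and item i is not yet met at the draw. If PCI is then not done, the patient has been sampled but is not eligible.

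A site that waits for item i before drawing blood enters only case (a). A site that draws at screening can also enter (b) and (c). Three hospitals take part, and the visible text does not tell them which to do.

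**Step 3: how many events carry the analysis.** The cited rate reproduces: 151/1864 = 0.0810, or 8.1%. Applied to this cohort:

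- 150 × 0.081 = 12.15, about 12 MACE.
- With 10% lost, 150 × 0.90 = 135 and 135 × 0.081 = 10.9, about 11.
- One event before the draw is 1/12.15 = 8.2% of the total.

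This assumes that the cited rate carries over to the plan's composite.

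**Step 4: illustration of dilution (assumptions not in the document).** Suppose a fraction f of samples is post-PCI, PCI shifts the marker by d SD, and position is unrelated to outcome. A standardised marker difference is then multiplied by 1/√(1 + f(1 − f)d²).

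| f | d = 0.5 | d = 1.0 |
|---|---|---|
| 0.25 or 0.75 | 0.977 | 0.918 |
| 0.50 | 0.970 | 0.894 |

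Dilution alone is modest, with 0.89 to 0.98 of the difference retained.

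**Step 5: if position is related to outcome.** Let f₁ and f₀ be the post-PCI shares in patients with and without MACE. The spurious difference is d × (f₁ − f₀) SD. The document gives none of d, f₁ or f₀, so neither size nor sign can be computed.

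**The case against.** The strongest reply is that this is a journal article. The order of sample and PCI may stand in the flowchart (Fig. 1), which I have not seen, or in a full protocol or laboratory manual. That stands as a limit: a reader might infer that the study does mix pre- and post-PCI blood, but the text only permits it. It does not remove the point, because the two rules that are stated use different clocks and the sampling rule as worded admits both orders.

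A reader might also infer that all 150 patients are affected, or that most STEMI samples are post-PCI and a sizeable part of the rest pre-PCI. The document gives no PCI times, so no such share is supported.

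Nor is there a contradiction between the population section (patients who "were diagnosed as ACS according to the guideline") and item i. Naming a source population and then narrowing it is ordinary drafting. Restricting to PCI patients also suits a composite that includes in-stent restenosis. What remains is that conclusions should carry that restriction.

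It is fair to say that no passage states that the procedure itself shifts these markers. The Discussion makes it plausible but gives no effect size. It is also fair that no reflow is secondary and can be seen at later angiography. The ordering problem is limited to the index procedure, but there it follows from the definitions alone.

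Finally, requiring a pre-PCI draw in every emergency patient would raise consent and feasibility problems. That is accepted, and the fix does not require it.

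**Conclusion.** The point holds as a mismatch between stated rules. Item i requires completed PCI, the sample is anchored only to admission, and samples on either side of PCI comply. Two consequences follow without any assumption about how markers behave: for a post-PCI sample, index no reflow precedes the marker, and so does any MACE component that occurred before the draw.

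Confounding by ACS subtype is possible but not shown. It needs PCI timing to differ by subtype and PCI to shift the markers. The shares, the size and the direction cannot be derived. With about 12 expected MACE (about 11 after losses), a few events on the wrong side of the draw would matter to the predictive analysis. This should be corrected, but it does not invalidate the design.

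**What to change.** 1. Reconcile the inclusion and sampling sections by stating the intended order of research sample and index PCI. Preferably take the sample with routine admission bloods before PCI, where consent and urgency allow and without altering care. If Fig. 1 already fixes the order, carry it into the text.
2. Record the times of sample and index PCI. The electronic medical record is already the data source and may hold both.
3. Flag post-PCI samples and leave them out of the index no-reflow analysis.
4. In the predictive MACE analysis, count only events after the draw.
5. Examine pre-/post-PCI status in a sensitivity analysis. About 12 events are too few to make it a compulsory covariate.
6. Report how many patients were sampled and did not go on to PCI.
7. Word conclusions as applying to ACS patients treated with PCI.

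The cost is protocol wording, two time stamps, a somewhat smaller no-reflow analysis set and slightly fewer countable in-hospital events. Items 2 to 7 remain useful if samples have already been taken, provided that the times can be recovered.

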### Exclusion criteria

i) Patients with dilated cardiomyopathy, hypertrophic cardiomyopathy, history of severe cardiogenic shock, active endocarditis, rheumatic heart disease, or severe valvular disease, severe hepatic or renal dysfunction, severe hemorrhagic diseases, severe infectious diseases, severe respiratory diseases, hematological diseases, autoimmune diseases and craniocerebral diseases, malignant tumors, pulmonary embolism, ventricular septal perforation and aortic dissection; ii) Patients with a serious medical condition or a life expectancy of less than 12 months; iii) Patients with a history of allergy to contrast media; iv) Patients contraindicated with antithrombotic therapy; v) Patients lack of medication compliance and could not take secondary prevention drugs regularly for CHD as required; vi) Patients participated in another clinical trial that had not yet completed or had completed for less than 3 months.

### Consent

Patients who do not meet the exclusion criteria and who meet all inclusion criteria may participate in this study. Researchers of the study including [name] and [name] will screen eligible patients for ACS diagnosis in the Chest Pain Center of multicenter and communicate with them or their agents about the general content of the study. These patients have every right to choose to participate in the study or not. These patients or their agents will be fully informed that participation in the study will not affect normal diagnosis and treatment, will not increase the risk of participants, and that participation or non-participation in the study will not affect patients' normal medical interests. However, participation in this study may provide new hope for improving the prognosis of patients with ACS. In addition, when patients or their agents agree to participate in the study, they could to choose how the clinical outcomes will be observed in different time point: by telephone, inpatient and outpatient medical records, or by contacting our researchers themselves and indicating on their informed consent. The dissemination of the results will occur through the publication of articles in international peer-reviewed journals, once the results are published, patients and their representatives will be notified by text or phone within a year. Those who agree to participate will sign informed consent.

### Primary outcomes

Primary outcomes of this cohort are major adverse cardiovascular events within 1 year, including in-stent restenosis, severe ventricular arrhythmia, heart failure, recurrent angina pectoris, and sudden cardiac death.

### Secondary outcomes

Secondary outcomes include the occurrence of these condition within 1 year: i)No reflow after PCI (after reperfusion treatment, blood flow of coronary artery is slowed down or completely absent); ii)Atrial fibrillation; iii) All-cause death except cardiovascular death; iv) Stroke/cerebrovascular accident.

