### Statistical analysis

The counting data were expressed as percentage and analyzed by χ2 test and non-parametric rank sum test. The measurement data were expressed as mean ± SD deviation. Student’s t-test was used for comparison of indicators. and P < 0.05 was considered statistically significant. Multivariate logistic stepwise regression analysis was performed on the statistically significant indicators to screen out the predictors of target outcomes. The receiver operating characteristic (ROC) analysis was used to analyze the selected predictors. The optimal cut-off point was found when the incidence of MACE was lowest by calculating the area, sensitivity and specificity under the curve, the optimal cut-off point was found when the incidence of MACE was lowest. The results were analyzed and discussed, the rationality of the results was analyzed in combination with the clinical practice and related literature, and the results were expected to have certain guiding significance for clinical work.

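### No-reflow seen at the index PCI can predate the blood marker, because sampling is tied to admission and the outcome is not split by when it was seen

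*Protocol article*

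**What the plan says.** All references are to the protocol article.

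- **Outcome and window (Secondary outcomes).** "Secondary outcomes include the occurrence of these condition within 1 year: i)No reflow after PCI", described there as "after reperfusion treatment, blood flow of coronary artery is slowed down or completely absent".
- **Operational definition (Table 2).** "No coronary reflow or slow flow is observed during PCI or coronary angiography reexamination". The definition has two routes: the procedure itself and a later angiogram.
- **Follow-up content (text with Tables 1 and 2).** "The content of follow-up also includes no reflow, atrial fibrillation". No-reflow is thus among the items followed from the hospital stay to 12 months after discharge.
- **Population (Inclusion criteria).** Patients have ACS "and went through PCI", with "Duration of onset of patients ≤ 2 weeks".
- **Marker timing (Blood sample and data collection).** "Peripheral blood samples of these patients were obtained within 24 h of admission". No other draw is described, and the text does not relate this one to PCI.
- **Analysis (Statistical analysis).** Indicators significant at P < 0.05 enter a stepwise logistic regression "to screen out the predictors of target outcomes". The sentence does not name the outcomes. The later cut-off sentence refers to MACE.
- **Aim (Aim of the study).** The markers are to be related to MACE at 1 year. No-reflow is not a MACE component.

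**The concern.** A baseline predictor has to be measured before the event it predicts. The draw is timed from admission, whereas the first route to no-reflow is timed from PCI, and nothing in the text fixes the order of the two. All patients have PCI, so the question arises for the whole cohort.

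The study's own rationale makes reverse causation plausible. The Discussion links myocardial necrosis after ACS to the innate immune response, which is what the flow cytometry panel is meant to capture. Failed reperfusion may therefore change the cells being counted. In patients sampled after PCI, a marker difference by no-reflow status could be an effect of no-reflow but be presented as a predictor of it. The STEMI third of the cohort could be the most affected if those patients reach PCI soonest, which is an assumption.

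**Working it through.** **Step 1: time order.** Reading the sampling rule against the two routes in Table 2 gives three cases.

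| Case | Blood draw | No-reflow seen | Order |
|---|---|---|---|
| a | before PCI | at index PCI or at repeat angiography | marker first |
| b | after PCI | at index PCI | outcome first |
| c | after PCI | first at repeat angiography | marker first |

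Only case b is a problem. The text permits it, has no rule to identify it, and puts it under the same label as a and c. The shares of the three cases cannot be derived from the article.

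**Step 2: illustrative size.** The plan gives no figure to reproduce. From the plan: N = 150 and a t-test at P < 0.05, taken as two-sided. The other inputs are assumptions:

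- no-reflow in 5%, 10% or 15% of patients: 0.05 × 150 = 7.5, 0.10 × 150 = 15 and 0.15 × 150 = 22.5, taken as n1 = 8, 15 and 22, with n0 = 150 − n1;
- a marker with no predictive value that rises by d = 0.3 or 0.5 SD after no-reflow;
- a share s of no-reflow cases that fall in case b: 1/3 or 2/3.

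The mean difference between groups is then s × d in SD units, and the t statistic has noncentrality s × d / √(1/n1 + 1/n0) on 148 degrees of freedom. The square root is 0.363, 0.272 and 0.231 for n1 = 8, 15 and 22. Two worked examples:

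- n1 = 8, d = 0.3, s = 1/3: 0.10 / 0.363 = 0.275, rejection rate 5.9%.
- n1 = 22, d = 0.5, s = 2/3: 0.333 / 0.231 = 1.44, rejection rate 30%.

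False-positive rate per marker:

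| n1 | d = 0.3, s = 1/3 | d = 0.3, s = 2/3 | d = 0.5, s = 1/3 | d = 0.5, s = 2/3 |
|---|---|---|---|---|
| 8 | 5.9% | 8.5% | 7% | 15% |
| 15 | 6.5% | 11% | 9% | 23% |
| 22 | 7.1% | 14% | 11% | 30% |

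The range is about 6% to 30% against a nominal 5%. As an extreme, if every no-reflow case were case b, d = 0.5 would give 28%, 45% and 58% for the three values of n1. The formula applies the average shift to all no-reflow cases. A simulation that shifted only the case-b patients agreed to within about 0.02.

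**The case against.** A reader might infer that no-reflow is always settled at the index PCI, so that every patient sampled afterwards has the outcome before the marker. The documents do not support that. Table 2 also accepts no-reflow or slow flow at repeat angiography, and the description in the outcome list says only that it follows reperfusion treatment. In case c the marker comes first.

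The 1-year label is not itself wrong either. Follow-up begins during hospitalization, so the window can hold both routes.

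Three further points carry weight:

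- **Use as a predicted outcome is inferred.** The stated aim ties the markers to MACE only, and no sentence says they will be tested as predictors of no-reflow. The inference is still reasonable: the regression sentence is not limited to MACE, no-reflow is a declared outcome, and no other analysis is given for the secondary outcomes.
- **The sampling order may be fixed elsewhere.** Fig. 1 carries the participant timeline and is not shown. A full protocol could also hold the clock times. If all blood were drawn before PCI, the problem would disappear. The text shown does not say so.
- **The size rests on assumed inputs.** At the low end (0.3 SD, one third of cases) the rate is 5.9% to 7.1%, little above nominal.

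What stands is case b. The repeat-angiography route does not cure it, because it pools events from before and after the marker under one name.

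**Conclusion.** The concern holds in a limited form. In patients sampled after PCI, no-reflow seen at the index procedure predates the marker, and the text has no rule to separate those cases from no-reflow that follows it. If the predictor search is applied to this outcome, a consequence of failed reperfusion could be reported as a predictor.

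The extent is unknown. The 6-30% range illustrates the assumptions in the working and is not an estimate for this cohort. The issue concerns one of four secondary outcomes and leaves the primary outcome untouched. It should still be corrected, because the change is cheap and the order cannot be restored later unless the times of PCI and blood draw are available.

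**What to change.** 1. Split no-reflow into two items: no-reflow or slow flow at the index PCI, reported as a procedural result, and no-reflow or slow flow first seen at repeat angiography, kept as a follow-up outcome. No case counted under Table 2 is dropped.
2. Record the clock times of PCI and of the blood draw.
3. Test markers as predictors of index-PCI no-reflow only in patients whose blood was drawn before PCI.
4. In patients sampled after PCI, report the marker difference by index-PCI no-reflow as an association only.

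The cost is a change of wording in the outcome list, Table 2 and the analysis section, plus two times that routine records should hold. No extra patients, visits or tests are needed. The drawback is fewer patients, and so less precision, in the analysis predicting index-PCI no-reflow.
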